### How missing data will be handled in the analysis {27c}

Missing data are expected to be minimal given the short follow-up period of 72 h. The primary analysis will be based on available cases in the FAS. However, if the proportion of missing data for the primary outcome exceeds 10%, a sensitivity analysis using worst-case scenario imputation will be performed to assess the robustness of the findings. Regarding time-to-delirium onset, participants who are discharged or die before 72 h without delirium will be treated as censored.

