### Sample size {19}

The sample size was determined on the basis of previous studies that investigated delirium prevention using orexin receptor antagonists and melatonin receptor agonists [8, 18]. One study reported a delirium incidence rate of 20.5% in the standard administration group (equivalent to the Passive PBPM group) compared with 7.4% in the early administration group (equivalent to the Active PBPM group). Another randomized controlled trial reported delirium rates of 16.7% and 0% in the placebo and suvorexant groups, respectively.

In this study, we anticipate a higher baseline incidence because the criteria include patients with nil per os status. Therefore, we estimated the incidence rates of delirium within 3 days of admission to be 25% in the Passive PBPM group and 5% in the Active PBPM group. To detect this difference with 80% power at a two-sided significance level of 5% (*α* = 0.05) using Newcombe’s method for the difference in proportions, 96 patients will be required. Accounting for a projected dropout rate of 10%, the target sample size will be set at 105 patients.

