### Sequence generation: type of randomization {21b}

Participants will be randomly assigned in a 1:1 ratio to either the Active or Passive PBPM group (Fig. 4). Stratification factors will include age (<75 vs. ≥75 years) and the baseline use of high-risk drugs for delirium.

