### Plans to promote participant retention and complete follow-up {25b}

Given the acute nature of the setting and the short follow-up period (72 h), high participant retention is expected. To ensure complete follow-up and minimize bias, the following strategies will be employed:

Retention Strategies: The PBPM intervention and assessments will be integrated into the standard clinical workflow of the emergency ward to minimize the burden on participants. Investigators and ward staff will monitor the participants’ clinical status daily to ensure adherence to the protocol.Data Collection for Discontinued Participants: If a participant deviates from or discontinues the intervention protocol (e.g., due to medical necessity, adverse events, or transfer to another ward), every effort will be made to continue the outcome assessments until the 72-h endpoint, provided that consent is not withdrawn.Outcome Data for Deviations: For participants who discontinue the study, the following data will be collected up to the point of discontinuation and included in the intention-to-treat (ITT) analysis:DRS-R98-JIncidence of agitation and medication recordsFinal delirium diagnosis by a psychiatrist (if possible, based on records up to the time of discontinuation)Withdrawal of Consent: If consent is withdrawn by the participant or their representative, all further data collection will cease. Data collected up to that point will be handled in accordance with the ethical approval and the participant’s preference.

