## Statistical methods

### Statistical methods for primary and secondary outcomes {27a}

The primary analysis will be performed on the FAS and repeated on the PPS as a sensitivity analysis. The incidence of delirium diagnosed using the DSM-5 within 3 days will be calculated for each group, with 95% confidence intervals (CIs). The between-group difference in incidence (Active PBPM minus Passive PBPM) and its 95% CI will be estimated using Newcombe’s method. Statistical significance will be set at a two-sided level of 5%. If the upper limit of the 95% CI for the difference is <0, the Active PBPM group will be considered to have a significantly lower incidence of delirium.

Unless otherwise specified, following secondary analyses will use a two-sided significance level of 5% and 95% CIs.Time to delirium: The time from enrollment to the onset of delirium (DSM-5) will be analyzed using Kaplan–Meier curves, with observations censored at 72 h.Delirium severity and sleep–wake cycle: Summary statistics for the worst DRS-R98-J severity scores and item 1 (sleep–wake cycle disturbance) scores recorded while the patient was awake will be compared between groups.

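### The worst-case check on missing primary outcomes runs only above 10% missing, although about 4% to 6% can be enough to remove significance

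*Protocol article*

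**What the plan says.** All section numbers refer to the protocol article.

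- **Missing data, {27c}.** The primary analysis uses the patients in the full analysis set (FAS) whose outcome is available. Beyond that, "if the proportion of missing data for the primary outcome exceeds 10%, a sensitivity analysis using worst-case scenario imputation will be performed". Discharge or death before 72 h is given a rule (censoring) for time to onset only.
- **Decision rule, {27a}.** Active is declared better "If the upper limit of the 95% CI for the difference is <0", by Newcombe's method, for Active minus Passive. The analysis is repeated on the per-protocol set (PPS).
- **Analysis sets, {27b}.** The PPS admits only FAS patients who followed the three-day protocol and whose primary outcome is complete.
- **Sample size, {19}.** The assumed incidences are "25% in the Passive PBPM group and 5% in the Active PBPM group", and "96 patients will be required". Then: "Accounting for a projected dropout rate of 10%, the target sample size will be set at 105 patients".
- **Retention, {25b}.** After a patient discontinues, "every effort will be made to continue the outcome assessments until the 72-h endpoint" provided consent stands. A psychiatrist's diagnosis from the records up to discontinuation is used if possible.
- **Eligibility, {14a}, and outcomes, {16}.** Patients who cannot stay more than 48 h are excluded, while the outcome window is 72 h.

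**The concern.** An available-case analysis is unbiased only if the missing patients resemble the observed ones within their arm. Section {15b} lists adverse events, clinical deterioration and death among the reasons for stopping the intervention. It is plausible, though not stated, that outcomes lost for such reasons are related to delirium and differ between arms.

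Worst-case imputation is the only planned analysis that tests this, and it is conditional. The PPS repeat drops the same patients and so cannot show whether they matter. If all 105 patients are in the FAS, 10 missing outcomes (10/105 = 9.5%) leave the check unused; the first count that triggers it is 11 (10.5%).

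The threshold should therefore be judged against how many missing outcomes could change the conclusion. If that number is well below 11, a significant result could be reported with its main vulnerability untested.

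**Working it through.** **Inputs.** Incidence 5% Active and 25% Passive, 96 evaluable patients, 10% dropout, 105 enrolled (section {19}); patients are "randomly assigned in a 1:1 ratio" (section {21b}); success if the upper Newcombe limit is below 0 (section {27a}). The event counts below are assumptions set close to the design rates.

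**Formula.** With Wilson 95% limits (l, u) for each proportion, upper limit = (pA - pP) + sqrt[(uA - pA)² + (pP - lP)²].

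**The plan's own figure.** Exact binomial enumeration of this rule at 5% versus 25% gives power 80.3% at 48 per arm and 79.3% at 47 per arm. The stated 96 is reproduced.

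**Expected events.** 48 × 0.05 + 48 × 0.25 = 2.4 + 12 = 14.4.

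**One example in full.** Observed 2/47 Active and 12/47 Passive: -0.2128 + sqrt[(0.1425 - 0.0426)² + (0.2553 - 0.1525)²] = -0.069, significant. Add 3 missing Active patients counted as delirium and 1 missing Passive patient counted as none, giving 5/50 and 12/48: -0.1500 + sqrt[(0.2136 - 0.1000)² + (0.2500 - 0.1492)²] = +0.002, not significant.

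**Other splits, by the same formula (Active v Passive).**

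| Missing (Active + Passive) | Share | Available cases | Upper limit | Worst case | Difference (points) | Upper limit |
|---|---|---|---|---|---|---|
| 3 + 0 | 3/105 = 2.9% | 2/50 v 13/52 | -0.074 | 5/53 v 13/52 | -15.6 | -0.010 |
| 4 + 0 | 4/105 = 3.8% | 2/49 v 13/52 | -0.072 | 6/53 v 13/52 | -13.7 | +0.012 |
| 3 + 1 | 4/98 = 4.1% | 2/47 v 12/47 | -0.069 | 5/50 v 12/48 | -15.0 | +0.002 |
| 2 + 2 | 4/100 = 4.0% | 2/48 v 12/48 | -0.068 | 4/50 v 12/50 | -16.0 | -0.015 |
| 3 + 3 | 6/102 = 5.9% | 2/48 v 12/48 | -0.068 | 5/51 v 12/51 | -13.7 | +0.010 |
| 5 + 4 | 9/105 = 8.6% | 2/48 v 12/48 | -0.068 | 7/53 v 12/52 | -9.9 | +0.051 |

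Every row lies below the 10% trigger. Significance is lost at about 4% when the losses fall mainly in Active and at about 6% when they are even. One more observed Active event lowers the threshold: 3/48 v 12/48 (upper limit -0.041) with 2 missing Active patients, 2/98 = 2.0%, becomes 5/50 v 12/48, upper limit +0.002.

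**Dropout allowance.** 105 × 0.9 = 94.5, below 96. Covering 10% loss needs 96/0.9 = 106.7, so 107. With 105 enrolled, 96 evaluable allows 9/105 = 8.6% loss. At 10% loss about 94 remain, 47 per arm, with power 79.3%.

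**The case against.** The strongest reply is that the imputation is extreme. It gives every missing Active patient delirium, against a design rate of 5%, and no missing Passive patient delirium. Milder assumptions keep significance:

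- If 2 of the 3 missing Active patients in the worked example are delirious, 4/50 v 12/48 has upper limit -0.022.
- With 10 missing, 5 per arm, of whom 2 Active and 1 Passive are delirious, 4/52 v 13/52 has upper limit -0.030.

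This stands as a caution on interpretation: worst case is a bound, not a forecast. It does not support the trigger, because the protocol itself chose this check and the open question is only when to run it. A tipping-point table shows the milder cases alongside the bound.

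Three stronger readings are tempting and the document does not support them.

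- **That missing data could reverse the result.** In every scenario above the estimate still favours Active, by about 10 to 16 points. Only significance is lost.
- **That the trigger equals the planned dropout, so the check is sure to stay unused.** Dropout and a missing primary outcome are different things. Section {25b} continues assessment after discontinuation or allows a diagnosis from records, so fewer outcomes than dropouts may be missing. Conversely, 94 evaluable of 105 means 11 missing (10.5%), which would set off the check if those losses are missing outcomes within the FAS.
- **That the 48-h stay criterion will produce many missing outcomes.** The protocol gives no length-of-stay figures, and a patient discharged at, say, 60 h might still be classified from records. That would be a shortened observation period, which is not the same as a missing outcome.

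**Conclusion.** The concern holds in limited form. The only check on missing primary outcomes is switched off at levels of missingness that can decide significance: about 4% to 6% under worst-case imputation at the design rates, depending on the split between arms, against a trigger above 10%. The per-protocol repeat does not substitute for it.

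This rests on observed counts near 5% and 25%, on worst case meaning Active missing counted as delirium and Passive missing as none, and on the full analysis set being close to the 105 enrolled. How many outcomes will actually be missing cannot be told from the document; the protocol expects few.

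The dropout allowance is a real but minor slip: two patients short of 107, and about one percentage point of power.

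**What to change.** In section {27c}, remove the 10% condition. State that whenever any primary outcome is missing, the worst-case analysis is reported with missing Active patients counted as delirium and missing Passive patients as no delirium, together with a tipping-point table over the possible numbers of events among the missing in each arm. The direction should be named, because it matters: with 9 missing split 5 and 4, counting all of them as delirium gives 7/53 v 16/52 and an upper limit of -0.017, against +0.051 under the direction above. The available-case primary analysis stays as it is. The cost is a little more analysis work, and the change can be made before the data are analysed.

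In section {19}, restate the allowance: either 105 enrolled covers 8.6% loss, or 10% loss leaves about 94 evaluable and about 79% power. This changes one sentence and not the target.

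The text should also reconcile the 48-h stay criterion in section {14a} with the 72-h outcome window in section {16}. No change to eligibility is proposed.

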### Methods for additional analyses (e.g., subgroup analyses) {27d}

Between-group differences in the incidence of agitation, behavioral and psychological symptoms of dementia (BPSD), and delirium incidence according to specific study drugs will be assessed using Newcombe’s method. The total dose of the rescue medication (hydroxyzine) will be summarized for each group.

### Interim analyses {28b}

No interim analyses are planned for this study. The trial will not be terminated early for efficacy. However, for safety monitoring, the principal investigator will continuously review all adverse events and serious adverse events, formally documenting any safety concerns identified during this process. The principal investigator, in consultation with the independent data center, may decide to terminate the trial prematurely if any unexpected and significant safety concerns arise or if the risk–benefit balance is deemed unfavorable. All such decisions, along with the underlying safety data will be reported to the IRB. The trial may also be terminated if recruitment becomes unfeasible.

### Protocol and statistical analysis plan {5}

This document serves as the primary protocol for the study. The detailed statistical analysis plan (SAP) is integrated within this protocol (see Statistical Methods {27}). The trial is registered at the Japan Registry of Clinical Trials (jRCT), and the registry information is available at jRCTs051220122. Any subsequent major updates or amendments to the protocol and SAP will be submitted as an update to this journal and updated in the jRCT.

## Oversight and monitoring

### Composition of the coordinating centre and trial steering committee {3d}

As this is a single-center study, the trial is managed with a streamlined structure to ensure quality and oversight:Trial Management Group (TMG): Composed of the principal investigator and co-investigators. They are responsible for the daily execution of the trial, including recruitment and protocol adherence. They meet annually (or more frequently as needed) to review the study’s progress.Data Coordinating Center: This center is responsible for generating the randomization sequence and allocation list. To ensure data integrity, they will provide monthly monitoring of the registration status and data entry throughout the trial period.Institutional Support: The Institute for Advancement of Clinical and Translational Science (iACT) provided expert consultation and administrative support during the study development phase, including advice on protocol design and the ethical review process.

### Composition of the data monitoring committee, its role and reporting structure {28a}

No formal data monitoring committee (DMC) was established for this study. As this is a single-center investigator-initiated trial with a short intervention period (72 h) and the pharmacological interventions are within the scope of standard clinical practice, the risks to participants are considered minimal. Instead, safety and trial progress will be closely monitored by the principal investigator and the Trial Management Group. Additionally, the Data Coordinating Center will perform monthly monitoring of registration and data entry to ensure study integrity.

### Frequency and plans for auditing trial conduct {29}

To ensure the highest standards of study conduct and data integrity, the trial will be subject to regular monitoring and auditing as follows:External Monitoring: An independent external monitor (not involved in the daily conduct of the trial) will perform an audit/monitoring visit once a year. This process includes verifying informed consent documentation, assessing adherence to the inclusion/exclusion criteria, and cross-checking the CRFs against source medical records (Source Data Verification).Internal Review: The Trial Management Group will conduct ongoing internal reviews of study procedures. Additionally, the Data Coordinating Center will provide monthly reports on the status of participant registration and data entry, allowing for the early detection of any procedural deviations.Audit Independence: The audit process will be independent of the investigators and the study funder to ensure objective oversight.

### Protocol amendments {31}

To ensure recruitment feasibility within the designated study period, the inclusion criteria and enrollment procedures were amended twice following study initiation. All changes were approved by the Institutional Review Board of Kyoto University Hospital.First Amendment (June 21, 2024, Version 4.0): Expansion of recruitment days. Initially, enrollment was restricted to patients admitted on weekdays (8:30–17:00). To improve the recruitment rate, this restriction was removed, allowing enrollment on weekends and public holidays within the same time window.Second Amendment (April 9, 2025; Version 5.0): Extension of the enrollment window. To accommodate patients admitted outside of regular working hours or at night, the enrollment window was expanded from the day of admission (day 1, until 17:00) to the following day (day 2, until 17:00). To maintain the integrity of the intervention, patients enrolled on day 2 will be excluded if they have already received any study medications (ramelteon, lemborexant, or blonanserin patch), rescue medications (hydroxyzine), or antipsychotics before enrollment.

The target sample size remained unchanged following these amendments.

## Dissemination policy {8}

The results of this study will be disseminated to ensure transparency and contribute to the improvement of clinical practice:Peer-reviewed Publications and Presentations: The findings will be submitted for publication in peer-reviewed international journals. Additionally, results will be presented at relevant domestic and international conferences (e.g., emergency medicine or psychiatry societies).Trial Registry: Within 1 year of study completion, a summary of the results will be reported on the Japan Registry of Clinical Trials (jRCT) website, which is accessible to the public.Communication with Participants: Since it may be difficult to contact participants directly after discharge, the results will be made available through public reporting and publications. If requested by a participant or their representative, an explanation of the study findings will be provided.Authorship: Authorship for publications will be determined based on the International Committee of Medical Journal Editors (ICMJE) recommendations.

## Discussion

This study addresses a critical gap in the management of older patients in emergency settings. Although the efficacy of individual pharmacological agents has been studied, the effectiveness of a system-based approach, such as PBPM, for prophylaxis is not well established. If the Active PBPM strategy proves effective, it can provide a practical model for delirium prevention that can be implemented in acute care hospitals, leveraging the expertise of pharmacists to reduce the burden on physicians and improve patient outcomes. One limitation of this study is its single-center, open-label design. However, diagnosis by psychiatrists (blinded to allocation) using the DSM-5 criteria and the use of a validated scale (DRS-R98-J) by nurses trained with standardized video materials help mitigate bias.

## Trial status

The current protocol version is 6.0, dated May 26, 2025. Recruitment began on November 25, 2022. Recruitment is currently ongoing and is expected to be completed by February 28, 2026. The final study completion is scheduled for March 31, 2026.

## Data Availability

The datasets used in this study are available from the corresponding author upon request.

## Abbreviations

AE: Adverse event
BPSD: Behavioral and psychological symptoms of dementia
CI: Confidence interval
CRA: Clinical Research Act
DSM-5: Diagnostic and Statistical Manual of Mental Disorders, 5th Edition
DRS-R98-J: Delirium Rating Scale-Revised-98, Japanese version
eGFR: Estimated glomerular filtration rate
FAS: Full analysis set
HCU: High-care unit
iACT: Institute for Advancement of Clinical and Translational Science
ICU: Intensive care unit
PBPM: Protocol-Based Pharmacotherapy Management
PPS: Per-protocol set
